**Discussion:**

The pathogenesis of IrAEs will be assessed through the MEDALLION cohort, with the potential to develop tools for their prediction and/or strategies for targeted prevention or treatment.

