### Study objectives

The study’s primary objective is to establish a clinically well-characterised and immune-phenotyped inception cohort of patients with cancer commenced on immune CPI therapy, thereby enabling the study of immune dysregulation that precedes IrAE development. In order to interrogate mechanisms of IrAE development we will focus on a range of biological measurements at baseline and during therapy, forming the basis of secondary and exploratory objectives. These will include the frequency and activation status of peripheral blood mononuclear cell (PBMC) subsets determined using multi-parameter flow cytometry, the gut and skin microbiome composition, serum cytokine mediators and, where possible, cellular composition of affected tissue.

The secondary objective of the study is to determine whether STAT3 phosphorylation (pSTAT3) in circulating CD4 + T cells of CPI recipients predicts IrAE development at baseline and/or following initiation of treatment.

The exploratory objectives of the study are:

(i)to determine whether baseline and/or dynamic changes in microbiome composition in the skin or gut precede IrAE development in CPI recipients.(ii)to identify immune cellular phenotypes whose dynamic frequency amongst CPI recipients predicts IrAE development.(iii)amongst CPI recipients who develop clinically significant colitis and/or skin dermatoses as adverse reaction(s) to treatment, to characterise immune infiltrates of lesional *versus* non-lesional tissue.(iv)to determine whether circulating cytokine profiles of CPI recipients predicts IrAE development at baseline and/or following initiation of treatment.

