#### Sample size justification

Observations made in a separate study, BIOFLARE [26], on pSTAT3 expression in a subset of circulating CD4 + T cells of RA patients in remission who develop disease flare following treatment cessation *versus* those who do not, were used as a basis for sample size calculation. Assuming CPI recipients with and without SirAEs will display a difference of similar magnitude in CD4 + T cell pSTAT3, enrolment of 66 participants with complete datasets will afford MEDALLION 80% power to detect a difference of ~ 24% between groups at alpha 0.05 (*pilot data used currently in preparation for publication; personal communication, [name] and [name]*). However, the longitudinal nature of our study is an important aspect, as it will allow taking account of the exact time the IrAEs occur. There are very few relevant similar datasets but one recent report found in a Swiss population three immune-related predictors of IrAEs in melanoma patients treated with CPIs: CXCL10, IL-10 and regulatory T cell (Treg) levels with hazards ratios of 12.6, 4.0 and 3.4, respecitvely [27]. Detecting effect sizes broadly similar to these with power 80% at significance level 0.05 requires a minimum of 21 events. Based on the anticipated 32% participants experiencing SirAEs, recruitment and following up of the aforementioned 66 patients will be sufficient for such analyses.

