#### Analysis plan

A broad range of measurable immune parameters will be evaluated in MEDALLION, in addition to the microbiome, but the aim of the main statistical analysis (secondary study objective) is to addresses the hypothesis that pSTAT3 expression in circulating CD4 + T cells pSTAT3 predicts SirAE development. The study design ensures that, in addition to testing a specific hypothesis, our unique cohort will form a substrate for a wide range of exploratory analyses in relation to cellular immunity and the microbiome during the development of SirAEs. Descriptive statistics will be used to describe recruitment rates, reasons for refusal to participate, refusal rates for optional procedures and missing data. They will also be applied to compare baseline circulating CD4 + T cell pSTAT3 between patients developing a significant SirAE *versus* those that do not (e.g. Mann-Whitney U test), with similar comparisons made up to the time of incident SirAE or matched time point. Exploratory analyses in relation to other biological parameters will then be undertaken in a similar manner. Markers’ association with time-to-SirAE will furthermore be evaluated using Cox proportional hazards regression. Significantly predictive markers will be graphically displayed by Kaplan-Meier curves after dichotomisation. Mixed effect logistic regression, a form of general linear mixed model (GLMM), will be applied to repeated measurements to test association between SirAE occurrence and marker longitudinal trends. Statistically significant trends will be depicted graphically. GLMM framework is flexible and will allow to exploratively adjust key clinical covariates although their number will be limited by available sample size.

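### Significance in an association test is treated as prediction of SirAE, although with about 21 versus 45 patients it is reached at an AUC of about 0.65

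*Protocol article*

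**What the plan says.** The secondary objective (Study objectives) asks whether pSTAT3 in circulating CD4+ T cells "predicts IrAE development at baseline and/or following initiation of treatment". Statistical considerations classes the secondary objective as hypothesis testing and the exploratory ones as hypothesis generating. The abstract's Discussion looks ahead to a study "with the potential to develop tools for their prediction and/or strategies for targeted prevention or treatment".

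The Analysis plan repeats the prediction hypothesis for pSTAT3 as its main aim. It then names a Mann-Whitney comparison of patients with and without SirAE, a Cox analysis ("Markers’ association with time-to-SirAE will furthermore be evaluated using Cox proportional hazards regression"), and a mixed-effect logistic model that tests association with longitudinal trends. Markers that come through are handled as follows: "Significantly predictive markers will be graphically displayed by Kaplan-Meier curves after dichotomisation".

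The Sample size justification gives two grounds for 66 patients. The group comparison "will afford MEDALLION 80% power to detect a difference of ~ 24% between groups at alpha 0.05". For time to event, published predictors are cited "with hazards ratios of 12.6, 4.0 and 3.4, respecitvely", and "Detecting effect sizes broadly similar to these with power 80% at significance level 0.05 requires a minimum of 21 events".

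**The concern.** Prediction and association are different claims. A test of association asks whether the marker's distribution differs at all between patients who do and do not develop SirAE. Prediction asks how well the marker separates them. The plan moves from the first to the second through the word *significantly*. It then selects the significant markers and draws them as two groups in the same single cohort that selected them.

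Two consequences follow. The study's one hypothesis-testing question could be answered yes by a marker that separates patients poorly. And the effects on display come from markers chosen because their estimates were large enough to pass, so they run high. Both matter because the study describes itself as a source of pilot data for later work, and its own sample size rests on hazard ratios taken from an earlier marker study.

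**Working it through.** **Inputs.** From the protocol article: 66 patients, 32% with SirAE, alpha 0.05, 80% power, hazard ratios 12.6, 4.0 and 3.4, follow-up up to 10 months. Assumed: 66 × 0.32 = 21.1, so 21 with and 45 without SirAE; two-sided testing (sidedness is not stated); 0.05 as the level behind *significantly* (it stands only in the Sample size justification); normally distributed markers.

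**1. The plan's own figure.** Schoenfeld's formula for the smallest cited hazard ratio with a 1:1 split: 4 × (1.96 + 0.842)² / (ln 3.4)² = 20.96, so 21 events. Power with 21 events is 80.1%. The stated minimum is reproduced.

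**2. Discrimination at the significance threshold.**
- Critical standardised difference: d = t(0.975, 64 df) × √(1/21 + 1/45) = 1.998 × 0.2643 = 0.528.
- AUC = Φ(d/√2) = Φ(0.373) = 0.646. The Mann-Whitney null variance gives nearly the same: 0.5 + 1.96 × √(67/(12 × 21 × 45)) = 0.5 + 1.96 × 0.0769 = 0.651.
- Hanley-McNeil SE at AUC 0.646 is 0.075, so the 95% CI is 0.646 ± 1.96 × 0.075, about 0.50 to 0.79.
- Sensitivity at 80% specificity: Φ(0.528 − 0.842) = 38%.
- At a median split of a marker with AUC 0.65: sensitivity about 65%, specificity about 57%, SirAE risk 41% in the upper half against 23% in the lower.

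**3. Discrimination at the effect detectable with 80% power.** The stated difference of about 24% comes without an SD, so the standardised effect is back-calculated: d = (1.96 + 0.842) × 0.2643 = 0.74. AUC = Φ(0.74/√2) = 0.70, SE 0.073, 95% CI about 0.56 to 0.84. Sensitivity at 80% specificity is Φ(0.74 − 0.842) = 46%, and PPV is 0.32 × 0.46 / (0.32 × 0.46 + 0.68 × 0.20) = 52%.

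**4. Inflation from selecting on significance.** Simulation of 66 patients (normal marker, exponential times, proportional hazards, censoring at 10 months, 32% events, 4,000 runs per row). The displayed values are medians among runs in which the continuous marker was significant in Cox regression.

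| True HR per SD (AUC) | Displayed HR per SD | True median-split HR | Displayed median-split HR |
|---|---|---|---|
| 1.30 (0.59) | 1.73 | 1.51 | 2.45 |
| 1.53 (0.64) | 1.82 | 1.94 | 2.59 |
| 1.84 (0.69) | 1.98 | 2.58 | 2.95 |

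The last row is the effect that 21 events detect with 80% power: exp(2.802/√21) = 1.84 per SD. A null marker that happens to pass shows a median-split HR of about 2.2 (2,000 runs).

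**5. Is the split to blame?** Ratio of displayed to true log hazard ratio, by row:
- kept continuous: ln 1.73/ln 1.30 = 2.09; ln 1.82/ln 1.53 = 1.41; ln 1.98/ln 1.84 = 1.12
- median split: ln 2.45/ln 1.51 = 2.17; ln 2.59/ln 1.94 = 1.44; ln 2.95/ln 2.58 = 1.14

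The two are nearly equal. The inflation comes from selection; the median cut adds almost nothing.

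**6. Conditional case.** If the cut were chosen to separate outcomes best, the displayed HRs in the three rows would be about 3.96, 4.14 and 4.66, and a null marker would reach log-rank p < 0.05 in about 28% of runs.

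**The case against.** The best defence is that the Kaplan-Meier curves are a display drawn after the Cox analysis. Nothing says that the Cox model uses a cut marker, or that a hazard ratio between the plotted groups is the reported estimate. This stands, so a claim that the test itself loses information is not supported.

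A reader might also infer that dichotomising exaggerates the effect, or that curves will show hazard ratios near 4. Step 5 rules out the first for a median split. The second needs a cut chosen on the outcome, which the text does not say.

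Nor is the absence of a discrimination measure or cut rule an error in itself: the article condenses a fuller protocol, and an analysis plan may exist. The point rests on what is written, namely that significance earns the label.

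Finally, the wider marker work is called hypothesis generating, the Discussion asks for validation of key findings, and the prospect of prediction tools is put only as potential. pSTAT3 is one pre-specified marker compared whatever its p-value, so for it selection decides only whether a curve is drawn. These points soften the selection concern. They leave untouched the gap between significance and prediction for pSTAT3, whose objective is hypothesis testing and worded as prediction. Later validation also does not correct inflated effects already used to plan it.

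**Conclusion.** The concern holds in a limited form. As written, a marker can be called predictive with an AUC of about 0.65 whose confidence interval reaches down to about 0.50. Even the effect detectable with 80% power corresponds to an AUC of only about 0.70. A significant result therefore does not answer the question that the secondary objective asks.

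Inflation among the displayed markers is real but depends on their strength: a true median-split HR of 1.51 would typically appear as 2.45, one of 2.58 as 2.95. It would be severe only with an outcome-chosen cut.

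These sizes rest on 21 versus 45 patients, two-sided 0.05, normal markers and, for the simulation, proportional hazards with exponential times. The point merits a change in the planned reporting; it does not show that the planned tests are invalid.

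**What to change.** - For pSTAT3, and any marker to be called predictive, report the AUC and Harrell's C with 95% CI, corrected for optimism by bootstrap wherever a model or cut is fitted. The AUC is the Mann-Whitney U divided by n1 × n2 (here 21 × 45 = 945), so it comes from a test already planned.
- Base any conclusion about prediction on these measures. Where only a test is significant, write *associated*.
- Report the hazard ratio per SD for pSTAT3 and for every marker tested. Doing so for the significant ones alone would leave the selection in place, since the continuous estimate is inflated as much as the split one.
- Show model-based SirAE risk at fixed percentiles of the marker (for example the 10th, 50th and 90th). If Kaplan-Meier curves are kept, use a cut fixed without reference to outcome, such as the median.

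The cost is a few sentences of plan text, slightly more analysis and a more modest headline. No extra patients or samples are needed.

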### Study design

MEDALLION is a single centre, prospective, longitudinal observational cohort study undertaken from the Northern Centre for Cancer Care, Newcastle upon Tyne, UK. All enrolled participants will receive treatment with combination or single agent CPI therapy routinely as standard care, remaining under study follow up for up to 10 months following CPI commencement or until they develop a “significant IrAE” (SirAE) defined according to pre-determined criteria specific to the affected tissue/organ system - whichever is sooner. In keeping with European Society for Medical Oncology (ESMO) practice guidelines, MEDALLION study-specific SirAE definitions generally align with CTCAE Grade 3, but are modified to reflect the significant impact of certain grade 2 IrAEs on quality of life, for example where warranting treatment with corticosteroids; they are summarised in Table 1.

**Table 1 Tab1:** Grades 2 and 3 IrAE definitions align with ESMO criteria [3]

Organ system(s)	MEDALLION definition of SirAE
Skin	Any grade 3 IrAE or above *or* CTCAE grade *≥* 2 IrAE, warranting topical/systemic steroids and/or (in guidance with consulting dermatologist) warranting diagnostic skin biopsy. *or* Physician-diagnosed new onset vitiligo
Gastrointestinal tract	Any grade 3 IrAE or above *or* Diarrhoea, CTCAE grade *≥* 2 persisting *≥* 3 days, warranting steroid treatment and/or endoscopically/histologically confirmed colitis. (Severity grade 2 is 4–6 liquid stools per day over baseline, or abdominal pain or nausea or nocturnal episodes) *or* CTCAE grade *≥* 2 hepatitis warranting steroids
Endocrine	Any grade 3 IrAE or above *or* Symptomatic autoimmune thyroid disease confirmed biochemically *or* Hypophysitis confirmed biochemically and/or radiologically
Musculoskeletal	Any grade 3 IrAE or above *or* Objectively observed inflammatory arthritis
All other	Any grade 3 IrAE or above

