**Fig. 2 Fig2:**
[figure not shown]
MEDALLION enrolment plan and design. Clinical assessments will take place at all patient visits, planned to coincide with routine hospital visits, and red arrows indicate time points at which 53 ml research bloods will be drawn (providing irAE has not occurred); additional research bloods +/- biopsy will be obtained at the time of incident SirAE)

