e Wherever possible the SirAE visit (and all of the listed procedures except optional gut biopsy) should be combined with the scheduled or unscheduled visit at which the SirAE is determined to have occurred, unless a scheduled or unscheduled visit has already been performed within post 7 days (or 14 days if a standard of care gut or skin biopsy with a research biopsy is being performed) of identification of the SirAE (see Sect. 7.7), in which instance the SirAE procedures should be carried out alone. Some of the SirAE procedures may require a separate visit when the SirAE event can only be confirmed when blood results are available or for gastrointestinal or skin SirAEs where the patient consents to gut or skin biopsy

f Optional ‘special case’ SirAE biopsies when standard of care gut or skin biopsy occur later than 14 days post initial identification of an SirAE whilst on CPI treatment. Optional research biopsies will be allowed at any time point that standard of care biopsies occur, until what would have been the patient’s final scheduled study visit if no SirAEs had occurred. Research procedures listed in the above table will be performed on the same day as the research biopsy (if not already performed within 7 days of the biopsy)

g Main study and (optional) for stool sample donation and also (optional) for a skin biopsy where indicated

h For obtaining gut biopsies for research from patients experiencing gastrointestinal SirAEs undergoing lower gastrointestinal tract endoscopies as part of routine care under direction of consulting gastroenterologist (optional), or for a skin biopsy where indicated (optional)

i Female patients will be asked whether they might be pregnant at each study visit and a pregnancy test conducted if relevant

j Physical exam as applicable, as per standard of care

k Symptom-directed questionnaire; Appendix 1

l FBC, U&E, LFT, TFT, Magnesium (standard of care tests) ESR, CRP (non-standard of care tests). At an End of Study visit FBC to be done as a research blood, if not being done as standard of care

m 4 × 10mL EDTA, 1 × 8.5mL serum, 1 × 10mL heparin

n. Skin swabs from forehead, upper chest, upper back, dorsum of the hand and forearm at each visit with potential additional swab from a site of vitiligo-like depigmenting rash if occurs. ***Skin swabs applicable only for up to the first 53 evaluable participants***

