### Follow-up: post-cycle 1,2,3,4, and 9 months

Patients undergo formal study clinical review post-cycles 1, 2, 3, and 4 months of CPI treatment and at 9–10 months depending on the CPI regimen as detailed in Table 2 to coincide with routine care visits to hospital. If patients change CPI therapy prior to completing the scheduled 6 study visits, then they can continue within the study from cycle 1 of their new treatment until they have completed 6 scheduled study visits in total. Adverse events and concurrent medications are recorded at each visit in addition to clinical review. Clinical review will include collation of a detailed symptom directed questionnaire from patients, general physical examination, collection of skin swabs and routine blood tests. Participants who have consented to optional stool samples will also provide these following each visit, they will furthermore be asked to submit a completed dietary questionnaire.

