### Withdrawal criteria

Participants can decide to withdraw their consent at any point during the study. The clinical investigator may withdraw a participant from the trial at any time if this is considered necessary, and for any reason including:

i.Symptomatic deterioration.ii.Participant withdrawal of consent or inability (through incapacity or otherwise) to provide consent for study-specific procedures to proceed.iii.Significant protocol deviation or non-compliance, including failure to attend for > 2 consecutive visits.iv.An adverse event such that continuation of CPI therapy is no longer appropriate, even if SirAE criteria are not fulfilled.v.Termination of the clinical trial by the sponsor.vi.Investigator’s discretion that it is in the best interest of the participant to withdraw.vii.The patient has fulfilled the SirAE criteria and completed their IrAE ad hoc visit.

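### The mixed-effects logistic model planned for marker trends does not suit SirAE, which happens at most once per patient and ends follow-up

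*Protocol article*

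**What the plan says.** The Analysis plan makes the prediction of SirAE by pSTAT3 in circulating CD4+ T cells its main statistical question. It lists three tools: group comparisons such as Mann-Whitney at baseline and up to the SirAE or a matched time point; a model in which each marker's "association with time-to-SirAE will furthermore be evaluated using Cox proportional hazards regression"; and, for trends, "Mixed effect logistic regression, a form of general linear mixed model (GLMM"), which "will be applied to repeated measurements to test association between SirAE occurrence and marker longitudinal trends". The last is the only tool assigned to trends and the only one for which covariate adjustment is mentioned.

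The design sections describe SirAE as a single event that ends routine observation:

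- Study design: patients are followed, "remaining under study follow up for up to 10 months following CPI commencement or until they develop a" significant IrAE, whichever comes first.
- Withdrawal criteria, item vii: "The patient has fulfilled the SirAE criteria and completed their IrAE ad hoc visit".
- Fig. 2 caption: red arrows mark "time points at which 53 ml research bloods will be drawn (providing irAE has not occurred"), with a further sample at the SirAE. The caption says irAE. The section on adverse events keeps patients with a non-significant IrAE in follow-up, so the SirAE must be meant.
- Follow-up section: patients who change CPI therapy continue "until they have completed 6 scheduled study visits in total", so a full series has six scheduled samples.

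There is one exception. Table 2, footnote f, states: "Optional research biopsies will be allowed at any time point that standard of care biopsies occur", and research blood is listed for that visit. This sampling is optional, limited to gut and skin biopsies, and comes after the event.

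**The concern.** A logistic model needs a binary response, and the only binary quantity in the sentence is SirAE. A random intercept in such a model is estimated from how binary responses cluster within patients who have several of them. Here a patient has either one fixed status (SirAE ever or never) or a run of zeros that may end in a single one. The article does not say which of these is the response, nor how a marker's trend enters as a predictor.

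The patient-level reading is a natural one, because the same section compares patients who develop a SirAE with those who do not. It is also the reading under which the model breaks down. The article adds that statistically significant trends will be shown graphically, so a test with the wrong error rate would feed directly into reported results on the study's one hypothesis-testing objective.

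**Working it through.** **Inputs from the protocol article.** About 66 patients and 21 SirAEs (32% × 66 = 21.1; Study population and Sample size justification). Six scheduled visits. Routine follow-up ends at the first SirAE.

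**The plan's own figure.** The minimum of 21 events belongs to the Cox analysis; none is given for the mixed model. With the smallest cited hazard ratio, 3.4, and assuming a two-sided test and an even split, Schoenfeld's formula gives 4 × (1.960 + 0.842)² / (ln 3.4)² = 31.40 / 1.498 = 20.96, so 21. It reproduces and is not in dispute.

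**Reading A: ever-SirAE status on every row.** Take the intercept-only case. Let p be the row-level probability given the random effect. A SirAE patient with k₁ rows contributes P₁ = E[p^k₁], and a SirAE-free patient with k₀ rows contributes P₀ = E[(1−p)^k₀]. Since p^k₁ ≤ p and (1−p)^k₀ ≤ 1−p, P₁ + P₀ ≤ 1. With two or more rows, equality requires p to be 0 or 1 for everyone, that is, an infinite random-intercept SD. The likelihood therefore approaches its maximum only as the SD goes to infinity. The limiting minus log-likelihood is

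21 × ln(66/21) + 45 × ln(66/45) = 24.05 + 17.23 = 41.28.

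Simulated data of this size follow the pattern:

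| Random-intercept SD | Simulation 1, minus log-likelihood | Simulation 2, minus log-likelihood |
|---|---|---|
| 0 | 201 | 177 |
| 5 | 61 | 61 |
| 20 | 45 | 44 |

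In a third simulation, with visit and marker as covariates, the SD ran to its permitted upper bound (exp(4) = 54.6) in all 120 fits. The nominal 5% likelihood-ratio test of the marker rejected in 28% of 60 studies with no marker effect and in 30% of 60 with a strong one. The exact percentages depend on where the optimiser is stopped, because no finite optimum exists. What matters is that the test hardly separates the two situations.

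**Reading B: SirAE yes/no at each visit, up to the event.** This is a discrete-time hazard model. With visit number, baseline marker and change from baseline as covariates (200 simulated studies per row, about 21 and 24 events):

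| True slope effect | Mixed logistic rejects | Ordinary logistic rejects | Random-intercept SD near 0 |
|---|---|---|---|
| none | 5.0% | 3.5% | 52% of fits |
| 1 log-odds per SD of slope | 46.5% | 46.5% | 54% of fits |

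The Monte Carlo standard error is √(0.05 × 0.95 / 200) = 1.5 points in the first row and √(0.465 × 0.535 / 200) = 3.5 points in the second. A separate simulation gave 8% and 47%. The test works, and the random intercept adds almost nothing.

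If only the concurrent marker value and visit are entered, the model tests level, not trend. In 60 studies without an effect, the mixed version then rejected in 11.7% and ordinary logistic regression in 6.7% (standard error 2.8 points at a true 5%).

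**Alternative: the marker as outcome.** A linear mixed model with a time-by-SirAE term rejected in 4% of simulated studies with no effect and 53% with one.

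**Assumed, not from the documents** (Reading B table and the 120 fits): marker intercept SD 0.7, slope mean 0.15 and SD 0.15 per visit, noise SD 0.5, per-visit event probability about 5 to 9%.

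**The case against.** The strongest reply is that this is a condensed article. Its Methods point to a full protocol as an online supplement, and outcome coding, time terms and the form of a trend are usually settled there or in the SAP. That stands for the coding: it may be defined elsewhere, and its absence here is not the point. But the article does name the model class, and a random-effects logistic model is the wrong class under one coding and nearly redundant under the other.

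Four stronger readings might be inferred, and the documents do not support them.

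- **That the model cannot test a trend under any coding.** Reading B does so at about the nominal error rate once change from baseline is entered.
- **That the model will always fail to converge.** This applies to Reading A. In Reading B a random-effect SD near zero simply gives ordinary logistic regression, which is interpretable.
- **That the serial samples would go unused.** The matched-time-point comparisons use on-treatment samples, and the Cox analysis uses event timing. The sample size rests on a group difference and an event count, not on the mixed model.
- **That a common on-treatment drift in the marker would create false associations.** A marginal logistic model with no time term, under an assumed common rise of about 1 SD, gave 12% false positives. A similar check over 1,000 studies with no effect gave 14.9%, which fell to 5.0% once visit was added; visit-level logistic regression gave 4.1%. The plan names no such marginal model and does not exclude a time term.

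Two further points stand. Blood from optional biopsy visits can follow the SirAE, so the event row is the last routine row but not always the last sample. And a linear mixed model for the marker is also exposed to series cut short by the event.

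**Conclusion.** The concern holds in limited form. The article pairs a model for repeated binary outcomes with an event that occurs at most once and stops routine sampling. With ever-SirAE status on every row, the random-intercept variance diverges and the marker test is not valid. With a visit-level indicator, the analysis is a legitimate discrete-time hazard model that overlaps the planned Cox regression; it addresses trends only if time and change from baseline or slope are specified.

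The divergence under the first coding follows from the structure of the data: it is shown exactly for the intercept-only model and by simulation with covariates. The rejection rates rest on assumed marker and hazard values and are illustrations. The study's primary objective, establishing the cohort, is untouched. What is affected is the trend analysis for the secondary, hypothesis-testing objective on pSTAT3 and the exploratory marker analyses handled in the same way.

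**What to change.** Replace the sentence on mixed-effects logistic regression with two analyses, each with a stated role.

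1. **Trends.** Fit a linear mixed model with the marker as outcome (for example log pSTAT3). Fixed effects: time since first dose, SirAE group, their interaction and CPI regimen. Random effects: patient intercept and slope. Use samples taken before the SirAE only, and test the group-by-time term.
2. **Prediction.** Fit Cox regression of time to SirAE with the latest pre-event marker value as a time-dependent covariate. An explicit discrete-time hazard model with visit terms is an acceptable alternative; if change is the question, enter change from baseline as a covariate.

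Add a joint model of marker and event time as a sensitivity analysis for series cut short by the SirAE. State that samples from post-SirAE biopsy visits are excluded from both main analyses.

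The cost is wording and a little more analysis work, with the same samples, the same data and standard software. Some sensitivity to event-driven truncation remains: a patient whose SirAE precedes the second visit has one pre-event sample and adds no slope information.
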